**7.9 Surveillance during the period of intervention**

A passive surveillance system to monitor malaria episodes in study children will be set up in the health centres within the catchment areas of the IPTc communities and in the district hospital.

Parents and guardians will be advised to come directly to a health centre if their child developed any symptoms or signs of illness. If the child has fever or any features suggestive of malaria, a finger prick blood sample will be collected for malaria parasite before treatment will be given. One slide will be prepared for each child and the slides will transported to a central laboratory for double reading and for definitive diagnosis. Those who test positive for malaria will be treated with oral quinine 10mg/kg 8hourly for 7days and will be followed on days 3 and 7 for outcome. Health centres with laboratory services, will collect blood sample for Hb. Children with Hb<8.0g/dl will receive treatment for anaemia. Every participating child who presents to the health facility for medication will be asked to produce an ID card. The information on the ID card will be compared with the master list held by the surveillance staff. Treatment at the health facility for malaria and anaemia will be free for all participating children.

Records will be kept of all admission and deaths of study children at the district hospital. A physician or a medical assistant and nurses on the ward will be asked to look out for any child with severe malaria, and any admission attributed to malaria will be carefully documented.

A surveillance supervisor will visit the health facilities fortnightly from June to October to supply logistics and collect completed record forms and prepared slides. At the same time s/he will visit IPTc coordinators to collect completed forms on community deaths. All deaths will be investigated using post-mortem questionnaire techniques and cause of death established wherever possible. The ID card will be used to confirm the identity of the deceased child and may provide some important information about the health and nutritional status of the child prior to death.

**7.10 IPTc dose regimens**

Treatment will be given during the months of June-July and September- October as follows: (AQ+SP), AQ (10mg/kg) daily for three days. SP will be given as a single dose [SP tablets containing 500mg sulfadoxine/25mm pyrimethamine will be given at a dosage of sulfadoxine (25 mg/kg) + pyrimethamine (1.25 mg/kg]. Tablets will be crushed, sweetened with sugar and mixed with water and administer orally to the children. The AQ+ SP regime was chosen because a recent study in Senegal showed that AQ+SP had the highest protective efficacy (Badara C. et al. Unpublished)

**7.11 Assessment of adverse Events**

***Eliciting and documenting adverse experiences***

All adverse events or reactions, which occur during the trial, will be documented. The nature of each experience, date and time (where appropriate) of onset, duration, severity and relationship to treatment will be established whenever possible.

***Serious Adverse Events***

A serious adverse experience is any event which is fatal, life threatening, disabling or incapacitating or results in hospitalization, prolongs a hospital stay or is associated with congenital abnormality, cancer or overdose (either accidental or intentional). Any serious adverse event that occurs within 24 hours of administration of chemoprophylaxis will be reported to the Local Safety Monitor, Chairman DSMB and director of GMP

***Data Safety Monitoring Board (DSMB)***

An independent committee will be appointed to oversee ethical and safety aspects of the study conduct. The main role of DSMB will be to review and analyse clinical safety data collected during the trial and to assess unexpected or serious adverse events (SAEs)

**7.12. Local safety monitor**

An experienced clinician will be appointed as the local safety monitor (LSM). The overall role of the LSM will be to support the clinical investigators and to act as a link between the investigators and the DSMB. All SAEs will be reported to him/her in his/her capacity as a liaison to the DSMB.

**7.13. Data Management and analysis**

All baseline, surveillance and laboratory data will be collected on forms designed for the trial.

Field and laboratory staff will be trained to follow procedures set out in the Standard Operating Procedures (SOPs.) Key data will be double entered using EPI info software and inconsistencies checked; range checks will be used for standard variables. Primary analysis will be compliance with IPTc between the five villages in the health centre group and those in the community group.

**6.0 Time Table of activities**

| **Activities** | **Duration** | **Start** | Months staring from January 2006 | | | | | | | | | | | | |
| --- | --- | --- | --- | --- | --- | --- | --- | --- | --- | --- | --- | --- | --- | --- | --- |
| 1 | 2 | 3 | 4 | 5 | 6 | **7** | **8** | 9 | 10 | 11 | 12 | 13 |
| High malaria transmission season | 6 months | May 06 |  |  |  |  | X | X | **X** | **X** | X | X |  |  |  |
| Development of proposal | 1 month | Jan. 06 | X |  |  |  |  |  |  |  |  |  |  |  |  |
| Submission to Ghana & LSHTM Ethics Committees | 3 months | Feb 06 |  | X |  |  |  |  |  |  |  |  |  |  |  |
| SOP/Field work (RCT) | 1month | Mar 06 |  |  | X |  |  |  |  |  |  |  |  |  |  |
| Order drugs | 2 months | Mar 06 |  |  | X |  |  |  |  |  |  |  |  |  |  |
| Recruitment and consent | 1month | April 06 |  |  |  | X |  |  |  |  |  |  |  |  |  |
| Training and sensitization | 2months | April 06 |  |  |  | X |  |  |  |  |  |  |  |  |  |
| Cross-sectional survey1 | 1 month | May 06 |  |  |  |  | X |  |  |  |  |  |  |  |  |
| Drug distribution | 4 months | June 06 |  |  |  |  | X | X |  |  | X | X |  |  |  |
| Passive surveillance | 6 months | June 06 |  |  |  |  | X | X | X | X | X | X | X |  |  |
| Data management | 6 months | June 06 |  |  |  |  | X | X | X | X | X | X | X | X |  |
| Cross-sectional survey2 | 1 month | Nov. 06 |  |  |  |  |  |  |  |  |  |  | X |  |  |
| Analysis and report writing | 6 months | Jan. 07 |  |  |  |  |  |  |  |  |  |  |  |  | X |

- 1. **Timetable and milestone for achieving objective**

###### *February 2006*

Submission to Ghana & LSHTM Ethics Committees

**March- April 2006**

Drugs and laboratory supplies procured

###### *April 2006*

Recruitment of study subjects completed.

**May 2006**

Pre- intervention **prevalence of malaria measured**

**November 006**

Post intervention prevalence of malaria and coverage of IPTc measured.

**January-Feb 2007**

Results of the study disseminated

**CONTRIBUTION TO THE OBJECTIVES OF THE GATES PROGRAMME**

**Indicate how this proposal meets the overall objectives of the Gates programme including capacity development in a malaria endemic country (maximum 100 words)**

**Training and Capacity Development:**

Amodiaquine plus artesunate combination is the leading option for Ghana for treatment of malaria. There is evidence that AQ+AS is an alternative to SP for IPTc. Obtaining evidence of efficacy of AQ+SP will provide an alternative to AQ+AS for IPTc before implementation as policy

**ETHICAL ISSUES**

**Discuss ethical aspects of the proposal.**

The protocol will be submitted to the London School of Hygiene & Tropical Medicine, and Ghana health service Ethics Committees for approval prior to the start of the trial.

Only those children whose parents give informed consent will be enrolled.

The study involves fingerpick blood samples from febrile children as part of routine patient care.

In addition, two finger prick samples will be obtained from all children in the trial during the cross-sectional surveys at the beginning and end of the intervention.

.

The study investigates an intervention appropriate to health needs of Ghana.

The drugs used for the trial are safe and have been used in Ghana.

Entry into the trial will not affect the health care of the participants.

Trial participants will receive free medical treatment during the period of intervention.

**Submission to LSHTM ethics committee Yes**

##### Will be submitted to LSHTM ethics committee prior to the start of the study.

**Submission to other ethics committee(s) (specify) Yes**

Will be submitted to Ghana government ethic committee prior to the start of the study.

**BUDGET (in £ sterling)**

|  | Year 1 |  |
| --- | --- | --- |
| **Personnel Cost** | ( in £) | Total (£) |
| Medical officer | 480 | 480 |
| Medical Assistants | 210 | 210 |
| Laboratory assistants | 600 | 600 |
| Laboratory technicians | 300 | 300 |
| Health facility surveillance supervisor | 150 | 150 |
| Community-based IPTc coordinators supervisors | 300 | 300 |
| Surveillance nurses | 480 | 480 |
| Drug distributors at health facility | 420 | 420 |
| Community IPTc Coordinators | 420 | 420 |
| Data Entry clerks | 480 | 480 |
| Rider | 60 | 60 |
| Driver | 60 | 60 |
| Data manager | 240 | 240 |
| Financial manager | 240 | 240 |
| **Sub Total** | **4440** | **4440** |
|  |  |  |
| **Patient care cost** | 3000 | 3000 |
| **Sub Total** | **3000** | **3000** |
| **Transport** |  |  |
| Fuel for Pick up | 800 | 800 |
| Fuel for motorbikes | 240 | 240 |
| Vehicle maintenance | 2000 | 2000 |
| Travel and Transport for EPI staff for drug distribution | 140 | 140 |
| Local travels | 1000 | 1000 |
| International travel | 2000 | 2000 |
| Communication | 500 | 500 |
| **Sub Total** | **6680** | **6680** |
| **Supplies** |  |  |
| Laboratory reagents, slides, slide boxes, lancets, and consumables | 1500 | 1500 |
| Cost of drugs for IPTc | 4000 | 4000 |
| Stationery | 500 | 500 |
| Desk top computer | 700 | 700 |
| Computing consumables | 800 | 800 |
| Procurement of microscope | 1000 | 1000 |
| Maintenance of microscopes and procurement of microscope objectives (X100), electronic thermometers, timers | 200 | 200 |
| **Sub Total** | **8700** | **8700** |
| **Cross-sectional survey** |  |  |
| Reading cross-sectional survey slides | 480 | 480 |
| Recruitment cross-sectional survey staff | 800 | 800 |
| **Sub Total** | **1280** | **1280** |
| **Other expenses** |  |  |
| Training cost for drug distribution | 120 | 120 |
| Training cost of surveillance staff and supervisors | 120 | 120 |
| Training cost of EPI staff | 36 | 36 |
| Training cost of research team members | 60 | 60 |
| Training cost for cross-sectional survey staff | 132 | 132 |
| Testing of study drugs | 150 | 150 |
| Reading passive surveillance slides | 175 | 175 |
| **Sub Total** | **793** | **793** |
| **Grand Total** | **24,893** | **24,893** |

**BUDGET JUSTIFICATION**

**Equipment**

The resources requested are for the proper conduct of the study in the Jasikan district of Ghana for one year. A desktop computer and is required for data entry. Two microscopes is required to provide laboratory support to the study.

**Personnel**

A medical officer is needed to help the PI with the study. A data manager is needed to ensure proper management of the data collected during the study. An accountant and a logistics and supplies officer are needed for proper accounting and management of logistics and funds. Two data entry clerks are needed for double entry of the data. One driver is needed to help with transportation of staff for community mobilization, conducting of surveys and monitoring of study subjects during of the study. A laboratory technician will be required for quality control. 10 community-based IPTc coordinators will be recruited for six months. Twelve field workers are needed to help with enumeration, sensitization and recruitment of study subjects and the cross-sectional surveys.

Five EPI nurses, 10 health centre staff, 10 surveillance nurses a disease control officer and a public health nurse from the DHMT will be required for the implementation of the study.

Four laboratory assistants from Hohoe DHMTs will provide laboratory support for the study

**Appendix 2**

**Jasikan IPTc delivery system**

**Screening & inclusion form for IPTc**

Sub-District ………………Community………………… date / / / /

**Child**

First Name…………………………….Last Name……………………………………

Date of birth[ ] Sex [ ] ]Weight(Kg) [ ]

**Mother/Guardian’s**

First Name………………………………Last Name…………………………………..

Age (in yrs [ ] Occupation…………………..

House No………Landmark………………………………………………………………

|  | **Inclusion criteria** | **Yes** | **No** |
| --- | --- | --- | --- |
| 1 | Age between 3 to 59 months |  |  |
| 2 | Resident in the community for at least the next six months |  |  |
| 3 | Has parent or guardian given consent |  |  |
| 4 | Child unable to take or retain medication |  |  |
| 5 | Existence of respiratory distress |  |  |
| 6 | Existence of serious or chronic illness |  |  |
|  | **Exclusion criteria** |  |  |
| 1 | History of drug allergy |  |  |
|  | **Measurement** | **Record measurement** | |
| 1 | Temperature |  |  |

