**7.2 Screening for eligibility**

Children whose parents or guardians wanted their wards to participate will be assessed by the research team for eligibility for enrolment into the study: Children with the following conditions will be excluded from the study: (1) severe malnutrition; (2) chronic diarrhoea; (3) history of convulsions; (4) prostration, extreme weakness (inability to stand or sit); (5) history of hypersensitivity to AQ or SP. The study staff will examine the children for these criteria at the time of pre intervention cross sectional survey and refer children having any of these conditions to the PI for the final decision.

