**Noticed any omission** [**Y] [N]**

If yes,

| Indicator | Circle Y or N |
| --- | --- |
| Verify child’s identity by asking for the project ID card | [Y] [N] |
| Compare ID number with the master list | [Y] [N] |
| Administer correct dosage for the child’s age | [Y] [N |
| Package correct dosage for day 2 and 3 | [Y] [N] |
| Advice care giver to come back for extra dose if the child vomits drug at home |  |
| Complete drug administration form after each | [Y] [N] |
| Indicate on the ID card for the month of child took the drug | [Y] [N] |

If there omissions

Action taken by the supervisor:

……………………………………………………………………………………………………

……………………………………………………………………………………………………

……………………………………………………………………………………………………

…………………………………………………………………………………………………..

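### Section 7.2 and the Appendix 2 screening form give different eligibility lists, and (a lesser point) section 7.10 and the Appendix 4 checklist give different dose bases

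*Protocol*

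**What the plan says.** **Eligibility.** Protocol section 7.2 states: "Children with the following conditions will be excluded from the study: (1) severe malnutrition; (2) chronic diarrhoea; (3) history of convulsions". The list goes on to prostration or extreme weakness and ends with "5) history of hypersensitivity to AQ or SP". On who checks and when, it says "The study staff will examine the children for these criteria at the time of pre intervention cross sectional survey", and children found with any of these conditions are referred to the principal investigator for the final decision.

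Appendix 2 is the screening and inclusion form. Six numbered rows stand under its inclusion heading. Rows 1 to 3 cover age, residence and consent. Row 4 reads "Child unable to take or retain medication", row 5 concerns respiratory distress, and row 6 reads "Existence of serious or chronic illness". The exclusion heading follows with a single row, a history of drug allergy. The form then asks whether the child is eligible and records enrolment status, delivery system and study number.

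**Dose basis.** Section 7.10 states the regimen per kilogram, for example "AQ (10mg/kg) daily for three days", with SP also in mg/kg. The Appendix 4 supervision form asks whether the distributor did the following: "Administer correct dosage for the child’s age".

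**The concern.** An eligibility form is the working version of the eligibility criteria. If its list differs from the protocol's, a screener who follows the form faithfully may not look for a condition that the protocol excludes, and nothing on the completed form would show that it was checked. Here the drug is given as prevention to children aged 3 to 59 months, so a missed exclusion is first a participant-safety matter. It also leaves the enrolled population, which is the denominator of the coverage proportion, without a single definition.

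The dose basis raises a smaller question of the same kind. Section 7.8 includes correct dosing in its adherence assessment, and the Protocol offers two references for what is correct.

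**Working it through.** No arithmetic beyond counting applies. The check sets the texts side by side.

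**Step 1: each section 7.2 exclusion against Appendix 2.**

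| Section 7.2 exclusion | Row on the Appendix 2 form |
| --- | --- |
| Severe malnutrition | None by name; row 6 may catch it |
| Chronic diarrhoea | None by name; row 6 may catch it |
| Past convulsions | None by name; row 6 does not clearly cover it |
| Prostration or extreme weakness | None by name; row 6 may catch it |
| Hypersensitivity to AQ or SP | Drug allergy, worded more broadly |

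Named on the form: 1 of 5. Not named: 5 − 1 = 4.

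**Step 2: each Appendix 2 row against section 7.2.** Of the 6 rows under the inclusion heading, 3 (rows 4 to 6) are illness or intolerance conditions, and section 7.2 names none of them. Six-month residence in row 2 is also absent from section 7.2. So neither list contains the other.

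**Step 3: is the placement an artefact of text extraction?** Probably not. The numbering runs 1 to 6 under the inclusion heading and restarts at 1 under the exclusion heading.

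**Step 4: is the gap closed elsewhere?** In part. Section 7.2 has study staff examine for its own criteria at the pre-intervention survey. Section 7.7, which describes that survey, mentions drug-allergy history, temperature and anthropometry. Anthropometry could reveal malnutrition; convulsions, diarrhoea and prostration are not mentioned, although the description need not be complete. The timetable puts that survey in May and completion of recruitment in April. Section 7.8 starts drug in June, after the survey, though section 7.1 lists May as a treatment month. Appendix 2 has no field for the referral or its outcome.

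**Step 5: dose basis.** Section 7.10 uses mg/kg for both drugs; the Appendix 4 item uses age. The text shown has no table linking the two. Section 7.5 says the identification card will carry age and enrolment weight, but the Appendix 3 card template has a field for neither, so it does not settle which basis the distributor works from.

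**The case against.** The strongest reply is that these are drafting slips with safeguards around them. Much of that stands, and it rules out several stronger readings.

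- *A reader might infer that the form alone decides who is enrolled.* The Protocol does not say so. Section 7.2 assigns the examination to study staff and the final decision to the principal investigator, and the form's eligibility question is a separate judgement.
- *A reader might infer that ticking yes on every inclusion row selects sick children.* The form states no scoring rule. Applied literally, that rule would admit only children with all three conditions and turn away every healthy child. A heading placed three rows too low is the more plausible explanation.
- *A reader might infer that four exclusions go wholly unscreened.* They are missing by name only. The general row on serious or chronic illness may catch some of these children; past convulsions is the item with no clear counterpart.
- *A reader might infer that screeners will apply different lists in different villages or arms.* Section 7.2 describes one research team, and the Protocol shows one form. Nothing points to variation by village or arm.
- *A reader might infer that the adherence endpoint will be misclassified.* The Appendix 4 item monitors the distributor's conduct. No section feeds it into the endpoint or has anyone recheck doses against weight. Age bands can also be a field version of weight-based dosing, and a conversion table could lie in pages removed from the copy reviewed, such as the text between Appendices 4 and 6.

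What remains is the mismatch itself. Good judgement, training or procedures may make up for it, but they should not have to override the form on which enrolment is recorded.

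**Conclusion.** The point holds as an internal contradiction to be settled before fieldwork. Section 7.2 and Appendix 2 are different eligibility lists: four of five protocol exclusions lack a named row, three of the form's six inclusion rows are illness or intolerance conditions that section 7.2 does not name, and the required referral has no field. A screener relying on the form could miss children whom section 7.2 excludes. The section 7.2 examination and the referral reduce that risk without removing it.

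The dose-basis mismatch is real in wording but carries less weight, since a conversion may exist in pages not shown.

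Neither effect can be sized: the Protocol gives no prevalence for the excluded conditions, and the text shown has no age bands. The definition of the primary endpoint and the sample size are unaffected. The conclusion assumes that the form is used as printed and that the row order in the text shown matches the original.

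**What to change.** 1. Reconcile section 7.2 and Appendix 2 into one eligibility list. Put each item on the form under the heading that matches its intended effect, and add a field for the principal investigator's decision on referred children. Which criteria belong on the list is for the investigators; this review does not treat either version as the correct one.
2. Reconcile the dose basis between section 7.10 and Appendix 4. If the two are meant to agree through a conversion, cite it in both places. Use the same basis when judging correct dosing under section 7.8. Which basis applies is again for the investigators.

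The cost is a short text edit and the reprinting of two short forms: Appendix 2 before recruitment in April 2006 and Appendix 4 before the first drug distribution. No change to design, sample size or primary endpoint is needed.

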**Is child eligible? [Yes] [No]**

**Enrolment status**

| Enrolled [ ] | Delivery System [ ] | Study ID number  [ ] |
| --- | --- | --- |
| Not enrolled [ ] |  | |

**Appendix 3**

**THE IDENTIFICATION CARD**

**COMPARISON OF TWO APPROACHES TO DELIVERING INTERMITTENT PREVENTIVE TREATMENT FOR MALARIA IN CHILDREN: A PILOT STUDY IN CHILDREN AGED BETWEEN 3-59 MONTHS IN THE JASIKAN DISTRICT.**

Study number (ID NO) _________

First Name ………………………Last Name…………………………………

DISTRICT**:** SUB-DISTRICT**:**

NAME OF COMMUNITY:

Study group: community-based [ ] Facility-based [ ]

DATE OF DRUG ADMINISTRATION: [1] / / [2] / / [3] / / [4] / /

**THE BEARER OF THIS CARD IS A PARTICIPANT IN THE ABOVE NAMED STUDY. TAKE FINGER PRINT BLOOD FOR HAEMOGLOBIN (HB) AND BLOOD FILM FOR MALARIA PARASITES BEFORE TREATING HIM/HER WITH THE RECOMMENDED DRUGS FOR CLINICAL MALARIA.**

**Appendix 4**

### Jasikan IPTc delivery system study

### Drug administration supervision monitoring form

Community ……………………….. Delivery system [ ]

**IPTc coordinator/ distributor:**

First name…………………………Last name……………………

**Noticed any omission** [**Y] [N]**

If yes,

| Indicator | Circle Y or N |
| --- | --- |
| Verify child’s identity by asking for the project ID card | [Y] [N] |
| Compare ID number with the master list | [Y] [N] |
| Administer correct dosage for the child’s age | [Y] [N |
| Package correct dosage for day 2 and 3 | [Y] [N] |
| Advice care giver to come back for extra dose if the child vomits drug at home |  |
| Complete drug administration form after each | [Y] [N] |
| Indicate on the ID card for the month of child took the drug | [Y] [N] |

If there omissions

Action taken by the supervisor:

……………………………………………………………………………………………………

……………………………………………………………………………………………………

……………………………………………………………………………………………………

…………………………………………………………………………………………………..

